**FIGURE 1 F1:**
[figure not shown]
Overview of the VT-ART study.

## Radiotherapy

Ventricular tachycardia ablation through radiation therapy will be administered through image-guided radiotherapy (IGRT) by a linear accelerator (Linac) (e.g., TrueBeam–Varian Medical Systems, Palo Alto, CA), an SBRT-dedicated Linac, including a dedicated Linac with gating delivery (e.g., TrueBeam Edge Linac, Varian Medical Systems, Palo Alto, CA) with 6 MV flattening filter-free photons and dose calculation algorithm Acuros (Eclipse Version 15.6.04 Varian Medical Systems, Palo Alto, CA), or a MR-guided Linac (i.e., ViewRay MRIdian). Selection of a specific Linac type for each patient will be addressed based on the best personalization achievable, after a multidisciplinary discussion of the patient-specific clinical background, needs, compliance, and technical possibilities. The target area (TA), in terms of the clinical target volume (CTV), set-up margin (SM), and internal target volume (ITV), will be determined for each patient on a 3D computer tomography reconstruction based on CT scan or MRI (not performed if the patient has no MRI-conditional ICD), 12-lead ECG data, and electroanatomical mapping (EAM).

Three-dimensional EAM will be performed by three different systems on the basis of availability of the three workstations [Carto 3 system, Biosense Webster Inc. (Diamond Bar, CA, USA), Ensite Precision Cardiac Mapping Navx, Abbott (North Plymouth, MN, USA), and RHYTHMIA HDx™ Mapping System, Boston Scientific, Copyright IBM Corporation (Marlborough, MA, USA)]. Electrical information from the EAM and information from imaging will be combined to build a volumetric target for VT-ART (2).

Electroanatomical mapping data will be fused with CT-reconstructed 3D models applying the previously described approach for non-invasive EAM, through a series of electrode strips (worn by the patient) containing 256 electrodes (BioSemi, Netherlands), with small radiopaque markers attached at the location of the electrodes, to assist with visualization on cardiac imaging. A gated chest CT scan with 3 mm axial resolution was obtained to provide patient-specific heart-torso geometry and the location of the body surface electrodes relative to the heart (1–3). Since there is still no unique, standardized approach for TA delineation for those clinical scenarios, after the anatomical definition of the cardiac areas to be irradiated by EAM, an indirect TA definition by manual delineation of the EAM on a four-dimensional gated simulation CT scan, independently double-checked by two different radiation oncologists and cardiologists referring to the same EAM, will also be allowed.

A 2–5-mm margin will be provided to the TA to determine the planning target volume (PTV). The prescribed dose will be 25 Gy in a single fraction to 80% isodose. A 4D-CT will be applied to account for respiratory motion and either cone-beam computed tomography (CBCT)-based or MR-guided Linac positioning with the addition of either breath hold (BH) or free-breathing respiratory gating, depending on the patient’s compliance. If BH could be applied, deep inspiration breath hold (DIBH) should be preferred, but mid inspiration breath hold (MIBH), mid expiration breath hold (MEBH), and deep expiration breath hold (DEBH) are allowed if more suitable for planning.

Volumetric modulated arc therapy (VMAT) will be applied by multiple partial arcs (PA) depending on the arrhythmogenic scar volume and morphology to cover the TA. If an MR-guided Linac is used, static intensity-modulated radiotherapy (IMRT) will be applied.

Dose constraints for organs-at-risks and dose to target will follow the indications from the AAPM report Task Group 101 for single-fraction SBRT (4).

Our trial will combine two IGRT procedures to increase safety: intra-fractional and inter-fractional motion management devices and procedures are mandatory to be used. Volumetric imaging (CBCT- or MR-guided) scans before delivering each PA with regard to inter-fractional monitoring. Intra-fraction monitoring through the gating system is also mandatory. Continuous intra-fraction monitoring through an optical surface monitor system (OSMS) will be applied if available (e.g., TrueBeam Edge Linac, Varian Medical Systems, Palo Alto, CA, USA). Online adaptive procedures will be applied for the MR-guided Linac.

## Outcome measures

The primary outcome is investigating the difference in overall cardiovascular survival among the group undergoing VT-ART and the one not exposed to the innovative procedure.

The primary efficacy endpoint is a statistically significant difference in overall cardiovascular survival between the group undergoing VT-ART and the one not exposed to the innovative procedure; this will be defined in months and calculated from the time of the last procedure (represented by the last RFA for the control group and VT-ART for the innovative one, respectively).

The secondary outcome is evaluating the difference in ventricular event-free (referred to VT/VF, appropriate shock or ATP as recorded by the ICD) survival after the last procedure between the two groups (i.e., the single or last RFA in the control group and VT-ART in the innovative group). The respective endpoint is a statistically significant difference in ventricular event-free survival (in months) after the last procedure between the two groups.

An additional secondary aim is to evaluate the reduction in the number of VT episodes compared to the pre-treatment period between the two dynamic cohorts that will be investigated.

Ventricular tachycardia recurrence will be defined as evidence of monomorphic VT at ICD interrogation (either self-limiting or terminated by appropriate shock therapy or ATP). The number of VT episodes, defined as VT burden, in the 3 months before and after the procedure will then be compared.

The respective secondary endpoint will be evaluated facing 3 months before the last procedure (i.e., either RFA or VT-ART) and 3 months after.

We did set a blanking period after VT-ART before evaluate the effect on VT burden; in a recent study by Kautzner et al., the authors supported the pre-clinical theorem of myocardial apoptosis (up to 3 months post-stereotactic ablation) followed by a creation of fibrotic lesion (6–9 months post-stereotactic ablation) in the irradiated region (5). Consequently, we propose a 3-month-blanking period after the procedure.

Since a blanking period of 3 months after the procedure will be applied, the secondary endpoint will evaluate the number of VT episodes interval accounted for the last 3 months before the procedure and of the 3–6 months after it.

Other secondary objectives include identifying the benefits of VT-ART on cardiac function, as evaluated through an electrocardiogram, echocardiographic, biochemical variables, and patient’s quality of life.

In particular, we will evaluate the reduction or suspension of antiarrhythmic drug use compared to the baseline and the improvement of cardiac parameters (such as LVEF, left ventricular end-diastolic volume/diameter, ventricular strain, end-systolic volume/diameter, RVEF, and TAPSE for right ventricular function).

Analyzed biochemical variables will include heart failure biomarkers, such as NT-proB-type natriuretic peptide (NTproBNP), troponin (hs-TnI), and inflammation markers, such as polymerase chain reaction (PCR), tumor necrosis factor-alpha (TNF-alpha), and interleukin 6 (IL-6).

Improvement in the patient’s quality of life will be assessed compared to the pre-treatment period using the SF36 scale.

The patient’s QoL will be assessed before and after VT-ART using the SF36 scale (6); the post-treatment score will be compared to the pre-treatment period’s one to assess potential improvement. The post-treatment QoL evaluation will be performed at 3, 6, and 12 months after VT-ART. Once centers join the consortium, the SF36 QoL scale will be offered (although not mandatory) to all patients undergoing RFA: Before and at 6 months after conventional therapy.

Secondary outcome analyses will investigate the improvement of QoL scores after VT-ART and how QoL scores change the comparison between VT-ART and RFA.

Further secondary outcome analyses will be developed through imaging: Contrast infusion MRI and CT scan will be performed as required but not mandatory (if not contraindicated due to ICD) in the experimental arm.

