### Statistical considerations and sample size for matched pair analysis

A descriptive analysis will summarize the total number and stratification of patients with RFA and VT-ART.

We will perform a comparative analysis between RFA and VT-ART in patients with structural heart disease and refractory VT. Each patient who will be treated by VT-ART will be compared with two patients in the control group treated with RFA and best standard care but without VT-ART, on the basis of the following matching factors: Etiology of cardiomiopathy (ICM, NICM, and ACM), ventricular arrhythmia presentations (sustained ventricular tachycardia; incessant sustained ventricular tachycardia; and electrical storm), diagnostic tools used for scar definition (CT, MR, EAM, and ECG), arrhythmogenic focus anatomical intracardiac location (on the basis of VE exit by ECG and by activation map of VT), TA volume (endocardial electroanatomic substrate mapping area/volume in all cases; and epicardial mapping area/volume in case of 3D epicardial electroanatomic substrate mapping), heart volume, heart-to-TA volume, rate number of previous RFA attempts, type of previous RFA attempts (endocardial and epicardial), time (in days) between the first RFA attempt and VT-ART, time (in days) between the last RFA attempt and VT-ART, previous percutaneous stellate ganglion blockade, time (in days) between the percutaneous stellate ganglion blockade and VT-ART previous use of amiodaron, NYHA group, LVEF, BMI, age, and gender.

As mentioned, applied matching factors are summarized in Table 2.

Continuous data will be expressed as mean ± standard deviation, as appropriate, for all variables collected from the entire population or specific subgroups. A comparative analysis for subsequent levels of qualitative variables through the chi-square test and quantitative variables (scores on quality of life) with the *T*-test will be performed.

Non-parametric tests will be provided where the population distribution does not have a known form (normal Gaussian).

The differences in baseline and follow-ups between the same group will be analyzed with repeated measures approach: using the Friedman test and MANOVA for continuous variables and McNemar or Cochran’s *Q*-tests for categorical ones.

The significance of the tests is fixed with *p* < 0.05.

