### Toxicity evaluation

Radiotherapy-related toxicity will be defined using the Common Terminology Criteria for Adverse Events (CTCAE) v5.0. All adverse events, regardless of the toxicity grade and all-cause mortality, will be reported in the final study. Patients will be re-evaluated at 2 years of follow-up for late-onset toxic effects.

The secondary safety endpoints for VT-ART include the evaluation of all adverse events, which are classified as follows:

•Acute, during the patient’s hospital stay;•Subacute, in the first 90 days from discharge;•Chronic, 6–12 months following discharge.

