### Follow-up

Follow-up will be conducted for 36 months after treatment administration.

Patients prospectively enrolled within the consortium and treated by VT-ART will undergo ICD interrogations for up to 36 months after enrollment.

After a blanking period of 3 months, regular ICD interrogations [with intracardiac electrogram (EGM) storage of VT/VF or appropriate shock or ATP] will be prospectively collected for patients treated by VT-ART at 6, 9, 12, 18, 24, 30, and 36 months after the VT-ART procedure.

The ICD interrogation will collect the events along the last 3 months ahead of each follow-up evaluation.

Patients prospectively enrolled within the consortium and treated by RFA will undergo the same follow-up schedule if possible according to the clinical patient’s need and compliance.

Patient data retrospectively collected within the consortium and treated by either RFA or VT-ART will be retrospectively extracted at the same time points of prospective follow-up.

The final analysis will be performed only for patients with available data for the mentioned time points, either retrospectively or prospectively collected.

Quality of life will be assessed before the procedure (for prospectively enrolled patients candidate to VT-ART and RFA) and at 3, 6, and 12 months after therapy. Improvement in the patient’s quality of life will be assessed compared to the pre-treatment period using the SF36 scale.

Patient follow-up will thus, briefly, include:

•ICD interrogation (with EGM storage of VT/VF) at 6, 9, 12, 18, 24, 30, and 36 months from treatment.•A total of 12-lead ECG at 3, 6, and 12 months.•Echocardiography at 3, 6, and 12 months.•QoL assessment using the SF36 scale (7) will be performed at 3, 6, and 12 months for patients undergoing VT-ART.•QoL assessment using the SF36 scale will be performed at 6 months for patients undergoing RFA.

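### Ventricular event-free survival lists only ICD-recorded events and does not fix how a death counts, so different readings of the endpoint give different results

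*Protocol article*

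**What the plan says.** All references are to the protocol article.

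- **Outcome measures, event:** the comparison is of "ventricular event-free (referred to VT/VF, appropriate shock or ATP as recorded by the ICD) survival after the last procedure between the two groups". The bracket names three things, all recorded by the device. Death is not one of them.
- **Outcome measures, form:** "The respective endpoint is a statistically significant difference in ventricular event-free survival (in months) after the last procedure between the two groups". It is therefore a time-to-event endpoint measured from the last procedure.
- **Outcome measures, primary:** "The primary outcome is investigating the difference in overall cardiovascular survival among the group undergoing VT-ART and the one not exposed". Cardiovascular deaths are counted there, in a separate endpoint.
- **Follow-up, schedule:** "ICD interrogation (with EGM storage of VT/VF) at 6, 9, 12, 18, 24, 30, and 36 months from treatment".
- **Follow-up, window:** "The ICD interrogation will collect the events along the last 3 months ahead of each follow-up evaluation".
- **Follow-up, analysis set:** "The final analysis will be performed only for patients with available data for the mentioned time points, either retrospectively or prospectively collected".
- **Toxicity evaluation:** "All adverse events, regardless of the toxicity grade and all-cause mortality, will be reported in the final study". This reports deaths but does not link them to the ventricular endpoint.

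Nowhere does the article say whether a death without a recorded ventricular event is an event, a censoring or a competing event for this endpoint. It describes no device readout after death.

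**The concern.** An endpoint called survival normally ends at death. Here the event list is confined to what the ICD records, and the collection plan depends on the patient reaching an interrogation. A patient who dies before month 6 has no scheduled readout. A patient who dies between later visits has no further one, so any terminal arrhythmia falls outside the planned data.

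Deaths are to be expected. The population has structural heart disease and refractory VT and is unsuitable for transplantation. Eligibility requires a life expectation of more than 1 year in the absence of VT, while follow-up runs to 36 months. The primary outcome is itself cardiovascular survival.

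If deaths are related to ventricular arrhythmia, removing these patients from the risk set or from the analysis also removes ventricular events, and removes more of them in the group with more deaths. The groups are not randomised, so equal mortality cannot be presumed. Arrhythmia control could then look better in a group partly because more of its patients died.

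**Working it through.** The plan gives no figure for this endpoint, so there is none to reproduce. The sample size of 149 rests on the VT burden control rate and is unaffected.

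**Step 1. The readings that the text leaves open** for a patient who dies with no collected ICD event:

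| Reading | Support in the article | Status of the patient |
|---|---|---|
| A | The word survival in the endpoint's name | Event at death |
| B | The event list taken literally | Censored at the last readout |
| C | The available-data rule under Follow-up | Dropped from the analysis |
| D | No rule states it | Counted event-free to the end |

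**Step 2. Inputs, all assumed.** The 12-month risk of a ventricular event is v = 0.50. This is the upper end of the 25 to 50% recurrence after RFA cited in the Discussion, used only as an illustration. The 12-month mortality is d = 0.10 to 0.25; the article gives no mortality figure. Hazards are constant and independent.

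**Step 3. Event-free proportion at 12 months.**

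- A, death as an event: (1 − v)(1 − d). With d = 0.10: 0.50 × 0.90 = 0.45. With d = 0.25: 0.50 × 0.75 = 0.375.
- B, death censored: 1 − v = 0.50, whatever d is.
- C, only patients alive at 12 months kept: (1 − v)(1 − d)/(1 − d) = 1 − v = 0.50. It equals B only because independence is assumed.
- D: 1 − CIF, where CIF = [h_v/(h_v + h_d)] × [1 − (1 − v)(1 − d)], h_v = −ln(1 − v) and h_d = −ln(1 − d). With d = 0.10: h_v = 0.693 and h_d = 0.105, so CIF = (0.693/0.798) × 0.55 = 0.477 and the result is 0.523.

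At the lower recurrence figure, v = 0.25 with d = 0.20, the results are 0.60 (A), 0.75 (B) and 0.775 (D).

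**Step 4. What the gap means.** The difference between A and B is 5 points (50 − 45) to 12.5 points (50 − 37.5). Under independence, B estimates the ventricular-event risk in the absence of death without bias, so this gap separates two estimands. It would become a loss of ventricular events only to the extent that deaths were arrhythmic and the device was never read. The article gives no information on that share.

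**Step 5. Two groups, constructed example.** Take ventricular events of 40% against 50% and deaths of 25% against 10%. Reading B gives 60% against 50%. Reading A gives 0.60 × 0.75 = 45% against 0.50 × 0.90 = 45%. The mortality figures were chosen so that the difference cancels. The example shows only that the reading can change the conclusion, not that it will.

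**The case against.** A reader might infer that a patient who dies, even of arrhythmia, is scored as free of events. The article does not support that. It states no scoring or censoring rule for this endpoint. The bracket defines a ventricular event, and the word survival leaves room for death to end the event-free time. The available-data rule, read literally, would exclude the patient rather than count a success. Every patient has an ICD, and a fatal VT/VF or shock that the device recorded would meet the definition if the device were read; nothing forbids such a readout. These objections stand.

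A reader might also take the relative gap, 1/(1 − d), or 11% to 33% for mortality of 10% to 25%, as the bias of the endpoint. It is not. It compares death censored with death as an event, under assumed mortality and independent hazards, whereas the worry about bias comes from dependence. That objection stands too.

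Two further arguments stand in part. The primary endpoint and the mortality report would reveal excess deaths, which limits the harm but does not make the secondary comparison interpretable by itself. Detailed censoring and competing-risk rules may sit in a full protocol or analysis plan not shown. Whether death belongs to an endpoint called survival is, however, part of the endpoint's definition, and the article gives that definition. Finally, preferring a composite over a device-only endpoint is partly a matter of choice; leaving the choice open is not.

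**Conclusion.** The point holds as a defect in a stated endpoint definition. The name of the endpoint, its event list, the interrogation schedule and the available-data rule do not agree on what happens to a patient who dies without a collected ICD event. The literal readings censor or drop that patient, and either can favour the group with more deaths if death and arrhythmia are related. That relation is clinically plausible here, but the article does not quantify it.

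On size, the illustration puts the readings 5 to 12.5 percentage points apart at 12 months, for 50% ventricular events and 10% to 25% mortality. It rests on assumed mortality and independent hazards, and it shows sensitivity to the definition rather than an error already made. Because the endpoint is secondary and cardiovascular deaths are counted in the primary, this should be corrected before analysis but does not undermine the study as a whole.

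**What to change.** In Outcome measures, state that ventricular event-free survival runs from the last procedure to the first of VT/VF, appropriate shock, ATP or death from any cause, in both groups. Report beside it the cumulative incidence of ventricular events with death as a competing event. Where a device readout after death exists, use the recorded event date. Make clear under Follow-up that, for this endpoint, the available-data rule does not remove patients whose later time points are missing because they died.

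The cost is a sentence or two in the definition and one supporting analysis. Cardiovascular survival in months already needs dates of death, and all-cause mortality is already to be reported. The downside is small: non-arrhythmic deaths enter the composite and overlap with the primary endpoint, but the competing-risk analysis shows them separately. The choice should be fixed before the deaths in each group are known.

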## Populations

Our aim is to enroll patients with structural heart disease, in whom the presence of a myocardial scar induces refractory monomorphic VT or ventricular fibrillation (VF), as documented by either implantable cardioverter defibrillator (ICD) appropriate shocks or anti-tachycardia pacing (ATP) at ICD interrogation. We will enroll patients with recurrent VT/VF episodes despite optimal medical therapy (i.e., class III antiarrhythmic drugs) and at least one previous attempt of RFA or patients in whom ablation is not feasible, because of contraindications to the procedure or of patient intolerance. Previous percutaneous stellate ganglion blockade is neither a requirement for inclusion criteria nor exclusive criteria that will be collected in the standardized data collection for potential subgroup analysis.

Eligibility criteria are summarized in Table 1.

**TABLE 1 T1:** Inclusion and exclusion criteria.

Inclusion criteria	1. Patients with structural heart disease and monomorphic VT refractory to optimal medical therapy and previous RFA attempts (minimum of one attempt RFA)
	2. Patients with contraindications to conventional ablation or not suitable for any non-interventional approach, refusing any surgical ablative attempt; or patients who have already undergone RFA with arrhythmogenic focus refractory to previous ablation procedures
	3. Age >18 years
	4. Candidates not suitable for heart transplantation

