## Methods/design

Our trial will investigate the effects of administering a single fraction of external beam radiation delivered through SBRT techniques at a dose of 25 Gy on patients with recurrent episodes of VT and in whom optimal medical therapy and previous RFA attempts have failed to provide benefit from VT burden control. We will perform matched pair analysis with dynamic cohorts. We will compare two groups of patients: One that has been treated by all the standard approaches but has not undergone VT-ART and a second group that has also received VT-ART. The entire enrolled group (by multicentric recruitment) will be stratified according to some predefined characteristics and analyzed by matched pair analysis, based on the characteristics of patients treated with VT-ART. Once a patient is enrolled to undergo VT-ART within the multicentric consortium, the search for two patients with similar feature profiles not undergoing VT-ART will be shared.

Matching factors taken into account are summarized in Table 2.

**TABLE 2 T2:** Applied matching factors.

Parameter type	Subgroup options
Etiology of cardiomyopathy*	ICM
	NICM
	ACM
Age*	
Gender*	
BMI	
LVEF*	
NYHA group*	
Ventricular arrhythmia presentations*	Sustained ventricular tachycardia incessant sustained ventricular tachycardia electrical storm
Arrhythmogenic focus anatomical intracardiac location	Based on VE exit by ECG and by the activation map of VT
Diagnostic tools used for scar definition	CT
	MR
	EAM
	ECG
TA volume*	Endocardial electroanatomic substrate mapping area/volume in all cases; epicardial mapping area/volume in the case of 3D epicardial electroanatomic substrate mapping
Heart volume	cc range
Heart-to-TA volume	cc range
Previous use of amiodaron	Y/N
Number of previous RFA attempts*	
Type of previous RFA attempts	endocardial
	epicardial
Unfeasibility to repeat RFA	Y/N
Local recurrence of TA (same area of last RFA)	Y/N
Previous percutaneous stellate ganglion blockade	Y/N

TA, target area by electroanatomical mapping; BMI, body mass index; RFA, radiofrequency ablation; LVEF, left ventricle ejecting fraction; *mandatory matching factor.

Figure 1 depicts the design of the VT-ART study.

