## Discussion and final considerations

Sustained monomorphic VT is a potentially life-threatening condition that often affects patients with structural heart diseases. VT recurrence poses a severe threat to health and quality of life. Long-term management of recurring VT relies mainly on ICDs, pharmacological control (i.e., class III antiarrhythmic), and RFA of the pathological arrhythmogenic substrate.

New long-term solutions are currently being sought for patients in whom VT is refractory to conventional treatment strategies or in whom it cannot be performed. In patients with structural heart disease, the rate of VT recurrence after RFA has been reported to be between 25 and 50% (8). Intrinsic technical aspects of the procedure (e.g., difficult anatomical location of the arrhythmic substrate) as well as patient-related factors (e.g., patient frailty) may limit RFA feasibility in a portion of the population. Patients with structural heart disease are often fragile and have a varying number of comorbidities. Therefore, procedure invasiveness could be a limiting factor in the choice of the best treatment strategy (9).

Cuculich et al. first investigated the efficacy and safety of stereotactic radiation for the ablation of VT in a five-patient case series, which was later followed by the publication of a phase I/II prospective study by the same authors, including 19 patients (1, 2). Both studies reported a statistically significant reduction (99.9 and 94%, respectively) in VT episodes after a blanking period of 4 weeks. Subacute and chronic treatment-related side effects ranged from asymptomatic pericardial effusion to radiation-induced pericarditis and pneumonitis and were successfully treated with corticosteroids. Since then, a growing number of scientific articles have been published on this matter.

Overall, VT-ART has been proven to be an effective and adequately safe intervention in other studies (10, 11). Its non-invasive nature makes it a safe alternative for patients who are not suitable for percutaneous RFA (9). Nevertheless, despite the promising results detected by sporadic reports, limited case series, and systematic reviews (12), we still do not know if and at what level VT-ART (and STAR in general) could significantly and effectively improve the clinical scenario of such complex malignancies.

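### A control's clock may start at his only RFA, yet the plan never says whether that RFA counts as a previous attempt, and such a control cannot meet inclusion criterion 1 at time zero

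*Protocol article*

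**What the plan says.** **Time zero.** Under Outcome measures, cardiovascular survival is counted from the last procedure, "represented by the last RFA for the control group and VT-ART for the innovative one, respectively". For ventricular event-free survival the starting point is "the single or last RFA in the control group and VT-ART in the innovative group". The second wording explicitly admits controls who have had only one RFA.

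**Eligibility.** Table 1, item 1 asks for "monomorphic VT refractory to optimal medical therapy and previous RFA attempts (minimum of one attempt RFA" as a minimum. The running text of Populations is wider: "at least one previous attempt of RFA or patients in whom ablation is not feasible".

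**Matching.** Table 2 (Methods/design) lists "Number of previous RFA attempts" and stars it as mandatory. Type of previous attempts is listed without a star. Nothing says whether a control's index RFA is included. The statistical section repeats the factor and adds the days from the first and last RFA to VT-ART, for which a control has no equivalent.

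**Groups.** Methods/design describes them as "One that has been treated by all the standard approaches but has not undergone VT-ART and a second group that has also received VT-ART".

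**Fallback.** Under Sample size, matching starts on all factors. If too few controls are found, it continues on the mandatory factors only, so the RFA count stays in force throughout.

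**The concern.** A matched comparison needs both patients to be at the same point in their disease when their clocks start. In the VT-ART group the last RFA lies in the past and its result is known. In the control group the last RFA is itself time zero and its result is still to come. The same word, previous, can therefore describe two different histories.

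The rule also decides who becomes a control. Centers search for controls from circulated patient profiles, partly in retrospective series, and two centers could count RFA attempts differently without either breaking the protocol. A later analysis plan cannot undo that selection. It reaches the primary endpoint as well as event-free survival and VT burden, because all are tied to the same index procedure.

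**Working it through.** The plan gives no figure on this point, so there is none to reproduce. The check compares the definitions and then adds one illustration.

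**Step 1. Failed RFAs at time zero.** Take a control with n RFAs in all, the nth being the index procedure. Before time zero he can have failed at most n − 1. A single-RFA control has n = 1, so he has failed 0 and does not meet item 1 at that moment.

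| Reading of the count | Control's count | Matched VT-ART patient's count | Failed RFAs at time zero (control vs VT-ART) |
|---|---|---|---|
| A. Index RFA counted, outcome unknown | n | n | n − 1 vs n |
| B. Index RFA counted, and VT must have proved refractory to it | n | n | n − 1 vs n; the control's nth failure comes after time zero |
| C. Index RFA not counted | n − 1 | n − 1 | n − 1 vs n − 1 |

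**Step 2. What each reading does.**

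- **A.** For n = 1 the comparison is 0 failures against 1. The control has just been treated with uncertain success, while the VT-ART patient has already failed the same-numbered procedure. This tends to bias against VT-ART.
- **B.** The control qualifies only because VT came back after his clock started. For event-free survival and VT burden, this selects controls on the outcome and favours VT-ART. The direction for cardiovascular survival is not determined by the documents.
- **C.** The histories align for n ≥ 2. For n = 1 the control's count is 0. He does not meet item 1, and he matches only a VT-ART patient with no RFA. The Protocol overview says VT-ART patients have had RFA or cannot receive it, so the pair joins a patient who could have RFA with one who could not.

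**Step 3. Illustration of size under A.** The Discussion states that "the rate of VT recurrence after RFA has been reported to be between 25 and 50" percent. So 100 − 50 = 50% to 100 − 25 = 75% of unselected controls would not recur after the index RFA, whereas the matched VT-ART patients have all failed theirs.

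Assume that individual recurrence risk follows a gamma frailty with mean 1 and variance t, and that VT-ART and RFA are truly equally effective. With r the recurrence rate and S = 1 − r:

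- cumulative hazard H = (S^(−t) − 1)/t, so 1 + tH = S^(−t);
- mean frailty of those who recurred = (1 − S/(1 + tH))/(1 − S) = (1 − S^(1+t))/(1 − S).

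Unselected controls have mean frailty 1, so this value is the apparent hazard ratio for recurrence at time zero (VT-ART vs control). Example: t = 1, r = 25% gives (1 − 0.75²)/0.25 = 0.4375/0.25 = 1.75.

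| Frailty variance t (assumed) | r = 25% | r = 40% | r = 50% |
|---|---|---|---|
| 1 | 1.75 | 1.60 | 1.50 |
| 0.5 | 1.40 | 1.34 | 1.29 |
| 0.1 | 1.09 | not computed | 1.07 |

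As t approaches 0 the ratio approaches 1.00.

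**Step 4. Other matching factors.** Table 2 also lists local recurrence in the area of the last RFA and unfeasibility of repeating RFA. Both bear on RFA failure and may reduce the offset. Neither is starred, so both drop out in the mandatory-only fallback. If the control's last RFA is the index procedure, his recurrence status is known only after time zero, and matching on it moves the design from A towards B.

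**The case against.** **The ordinary meaning of previous is before the index procedure, so k matches k.** This is a fair reading, and it removes the offset for controls with two or more RFAs. It does not help the single-RFA control that Outcome measures admits, and the group description in Methods/design points towards counting all of a control's RFAs. The word single appears only for the secondary endpoint, but the primary endpoint's last RFA does not exclude such a patient.

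**Item 1 requires refractoriness, so a counted index RFA must have failed.** This is correct as a reading of the criterion. It rules out treating reading A as established, but it leads to B, which selects controls on a later event.

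**Other matching factors deal with it.** Partly. They may reduce the difference while matching on all factors is in force, but not in the fallback.

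**The hazard ratios are assumption-driven.** This stands. No frailty variance appears in the documents, and mandatory matching on LVEF, NYHA group, etiology, presentation, target-area volume, age and gender should lower what remains. The ratios also apply at time zero and would shrink over follow-up.

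**A condensed article leaves such definitions to the full protocol or CRF.** A bare data definition could be left there. Here, however, the article itself fixes time zero, eligibility and the mandatory factor, and for a single-RFA control those three do not fit together.

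**Conclusion.** The point holds as an unresolved conflict between time zero, inclusion criterion 1 and the mandatory RFA count. A control whose only RFA is the index procedure cannot meet item 1 before time zero, and each available reading of the count creates a problem for him. It should be settled before controls are selected, because it determines who they are.

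A reader might infer more: that matched patients always sit one failed procedure apart, that the bias runs against VT-ART, and that it amounts to a hazard ratio of 1.29 to 1.75. The documents do not support that. The offset belongs to reading A (and, in another form, B), and the plan does not state which reading applies. B pushes event-free survival and VT burden the other way. The hazard ratios illustrate A only, with the frailty variance and equal treatment effects both assumed, and fall to about 1.07 to 1.09 at a variance of 0.1. For cardiovascular survival no figure can be given, since its link to recurrence is not in the documents.

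**What to change.** 1. In Table 2 and the statistical section, define number and type of previous RFA attempts in both groups as attempts before the index procedure. A control's index RFA is not counted.
2. State that eligibility and all matching factors are assessed before time zero in both groups, using only information available by then. A VT-ART patient with k failed RFAs is then matched to controls with k failed RFAs before their index RFA.
3. Reconcile the word single in Outcome measures with Table 1. Keeping single-RFA controls just for VT-ART patients with no RFA would not settle it, because such a control still does not meet item 1 at time zero.

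**Cost.** Protocol wording and one derived CRF field. The real price is a smaller control pool: single-RFA patients can no longer be matched to VT-ART patients with a failed RFA. That makes the accrual rules under Sample size more likely to apply, both the move to mandatory-only matching and the closure without analysis below a 1:1 ratio.
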